#### Secondary endpoints

- Difference between the number of grade 3 and grade 4 adverse events between the intervention and control group during treatment, with special attention for: progression of respiratory insufficiency, thrombotic events, pulmonary embolism or deep venous thrombosis, bleeding, renal insufficiency, cardiac decompensation, liver enzyme abnormalities and/or liver failure
- Serum PIVKA-II levels before and during vitamin K supplementation in intervention versus control patients

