#### 8.1.2 Secondary study parameters/endpoints

- Difference between the number of grade 3 and grade 4 adverse events between the intervention and control group, with special attention for: progression of respiratory insufficiency, thrombotic events, pulmonary embolism or deep venous thrombosis, bleeding, renal insufficiency, cardiac decompensation, liver enzyme abnormalities and/or liver failure.
- Changes in serum PIVKA-II levels during COVID-19 with or without vitamin K supplementation

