#### 8.1.3 Exploratory study parameters

- Serum (undercarboxylated) protein S levels before and after vitamin K supplementation
- Incidence of respiratory failure defined as either intubation and mechanical ventilation or death (with respiratory failure as a likely direct or indirect cause of death) in the intervention versus control group
- Change in disease severity as measured by low-dose chest CT at baseline and on day 5 in intervention versus control groups
- Plasma levels of active MGP before and after vitamin K supplementation
- Normative APC sensitivity ratio and prothrombin (Echis Carinato test) and TFPI concentration before and after vitamin K supplementation
- Inflammatory parameters including CRP, d-dimer, ferritin, IL-6, TNF- $\alpha$ , IFN- $\gamma$  and s-IL-2r as measured by ELISA or Multiplex in both intervention and control groups
- Other markers related to the pathogenesis, susceptibility and severity of COVID-19 in both intervention and control groups
- Vitamin K epoxide reductase complex subunit 1 (VKORC-1) gene polymorphisms and vitamin D receptor gene polymorphisms

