#### **8.3.3 Follow-up of adverse events**

Adverse events will be monitored until discontinuation of treatment, at 28 days post inclusion mortality will be assessed.

When recording adverse events special attention will be paid to progression of respiratory insufficiency, thrombotic events, pulmonary embolism or deep venous thrombosis and bleeding. Toxicities will be scored according to the most recent version of the NCI Common Terminology Criteria for Adverse Events (CTCAE) version 5 (see Appendix).

The treating physician will determine whether adverse events require additional testing, such as, for example, pulmonary CT angiography in the case of suspected pulmonary embolism or coagulation parameters in the case of bleeding.

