### 9.2 AEs and SAEs

#### 9.2.1 Adverse events (AEs)

Adverse events are defined as any undesirable experience occurring to a subject during the study, whether or not considered related to the experimental intervention. All adverse events reported spontaneously by the subject or observed by the treating physician, the investigator or the research nurses are recorded into the patient's medical files.

Given the expected large number of adverse events occurring in patients admitted with COVID-19, only grade 3 and 4 adverse events will be reported in the Electronic Case Report Forms (eCRFs). Grade 3 and 4 adverse events will be recorded if they begin or become more severe between the time of the first treatment and discontinuation of treatment.

The severity of any adverse events, including any lab abnormality, will be determined by using the Common Terminology Criteria for Adverse Events, version 5 (NCI CTAE, appendix 1). The criteria are also available online at <http://ctep.cancer.gov>.

In any case where the NCI CTCAE criteria do not apply, severity should be defined according to the following criteria:

**Mild (grade 1):** awareness of symptoms that are easily tolerated and do not interfere with usual daily activity

**Moderate (grade 2):** discomfort that interferes with or limits usual daily activity

**Severe (grade 3):** disabling, with subsequent inability to perform usual daily activity, resulting in absence or required bed rest

**Life threatening (grade 4):** immediate risk of death from the reaction as it occurred

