### 9.2.2 Serious adverse events (SAEs)

A serious adverse event is any untoward medical occurrence or effect that:

- results in death;
- is life threatening (at the time of the event);
- requires hospitalisation or prolongation of existing inpatients' hospitalisation;
- results in persistent or significant disability or incapacity;
- is a congenital anomaly or birth defect; or
- any other important medical event that did not result in any of the outcomes listed above due to medical or surgical intervention but could have been based upon appropriate judgement by the investigator.

An elective hospital admission or outpatient visit will not be considered as a serious adverse event.

The investigator will report all SAEs to the sponsor without undue delay after obtaining knowledge of the events.

As symptoms in COVID-19 patients are often progressive after admission, an adverse event that prolongs hospitalization will only be considered a serious adverse events if, according to the investigator, it falls outside the natural progression of COVID-19.

Serious Adverse Events (SAEs) will be reported from the first study-related procedure until discharge from the hospital (at which time treatment will be discontinued) or until study day 28 if the patient is still admitted at that time. SAEs will be followed up for every patient on study day 28.

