### **10.2 Secondary and exploratory study parameters**

Adverse events will be compared by tabulating all grade 3 and 4 adverse events for each patient and calculating the proportion of in each group. The incidence of complications will be compared between groups with the chi-square test or Fishers exact test.

In the exploratory analyses, we will assess differences by comparing mean values between the groups using either a two-tailed student's t-test or non-parametric equivalents, paired if pre-treatment values are compared with post-treatment values, unpaired if comparisons are made between groups. For discrete variables (e.g. the number of positive assays), the chi-squared test or Fisher's exact test will be used (two-tailed).

As an exploratory analysis data will also be visualized on an individual patient level to evaluate the progression or correction of vitamin K deficiency in relationship to other parameters associated with COVID-19 disease severity.

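### The secondary safety endpoint stops at grade 4, so an event that is fatal without an earlier grade 3 or 4 record is left out of the between-arm comparison

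*Protocol*

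**What the plan says.** - **Endpoint.** Section 8.1.2 lists as a secondary endpoint the "Difference between the number of grade 3 and grade 4 adverse events between the intervention and control group". The summary has the same endpoint and adds a time window: "Difference between the number of grade 3 and grade 4 adverse events between the intervention and control group during treatment". Both single out thrombotic events, pulmonary embolism and bleeding, among others, for special attention.
- **Data capture.** Section 9.2.1 states that "only grade 3 and 4 adverse events will be reported in the Electronic Case Report Forms (eCRFs", for events that start or worsen between first treatment and the end of treatment.
- **Analysis.** Section 10.2 plans "tabulating all grade 3 and 4 adverse events for each patient and calculating the proportion of in each group". A further sentence says that the incidence of complications will be compared by chi-square or Fisher's exact test. Complications is not defined.
- **Scale.** Section 8.3.3 uses the "NCI Common Terminology Criteria for Adverse Events (CTCAE) version 5". Where those criteria do not apply, 9.2.1 supplies a scale whose top category, grade 4, is "immediate risk of death from the reaction as it occurred".
- **Death elsewhere.** An event that "results in death" is a serious adverse event (9.2.2). Mortality is checked at day 28 (sections 3, 8.3.3 and 8.6). The only endpoint in 8.1 that names death is an exploratory composite in 8.1.3, limited to "death (with respiratory failure as a likely direct or indirect cause of death".

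**The concern.** Endpoint, eCRF rule and analysis all name grades 3 and 4 and stop there. Grade 4 on the protocol's own scale describes a patient at risk of dying, not one who has died. A fatal event with no earlier grade 3 or 4 record therefore has no place in the comparison, although it may be of a type that the endpoint singles out.

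The direction matters. Each uncounted death lowers the apparent event rate of the arm in which it occurs. A death also ends the period in which that patient could have had further grade 3 or 4 events. Both effects favour the arm with more deaths. In a 40-patient phase 2a trial, readers will look at the counts and their direction rather than at a p-value, and a misleading direction would be carried forward.

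This is not a detail for a later analysis plan. The protocol itself fixes the endpoint and what is captured for it, and an analysis plan would inherit both.

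**Working it through.** The protocol states no figure on this point, so there is none to reproduce. The check has two parts.

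**1. Where does a fatal event go?** Take a patient with no grade 3 or 4 record who dies suddenly of a bleed during treatment.

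| Route | Is this death counted or compared? |
|---|---|
| Adverse event rule for the eCRF, 9.2.1 | No: grades 3 and 4 only |
| Secondary endpoint, summary and 8.1.2 | No: grades 3 and 4 only |
| Grade 3 and 4 tabulation, 10.2 | No |
| Incidence of complications, 10.2 | Unclear: term undefined |
| Exploratory composite, 8.1.3 | Only if respiratory failure is judged a likely direct or indirect cause |
| Serious adverse event reporting, 9.2.2 | Recorded; not listed as an endpoint in 8.1 |
| Safety Monitoring Committee, 9.5, 9.5.1 and 10.3 | Yes, by arm, after 20 patients and at study end; monitoring, not endpoint analysis |
| Day-28 mortality, sections 3, 8.3.3 and 8.6 | Recorded; not listed in 8.1, and no comparison named in 10.1 or 10.2 |

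The death is recorded and monitored, but it is missing from the listed safety endpoint with a planned between-arm analysis.

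**2. What can that do to the comparison?** The arm size is n = 20 (section 8.2: 20 boxes of each product). For each arm let x be the patients with a grade 3 or 4 record, and f the patients with a fatal event and no such record.

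- Rate as written: x/20.
- Rate with fatal events included: (x + f)/20.
- Each uncounted death lowers its arm's rate by 1/20 = 5 percentage points, so the difference between arms A and B shifts by (f_A − f_B)/20.

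The protocol gives no event rates, so the counts below are assumptions.

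| Arm A (x + f) | Arm B (x + f) | As written, A v B | Fatal included, A v B |
|---|---|---|---|
| 5 + 3 | 7 + 0 | 25% v 35% (Fisher p = 0.73) | 40% v 35% (p = 1.0) |
| 4 + 4 | 6 + 1 | 20% v 30% (p = 0.72) | 40% v 35% (p = 1.0) |
| 6 + 2 | 7 + 0 | 30% v 35% (p = 1.0) | 40% v 35% (p = 1.0) |

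In the first row the shift is (3 − 0)/20 = 15 points, from −10 to +5. In all three rows the direction reverses. None of the differences is near significance.

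If both arms truly have 8/20 = 40% of patients at grade 3 or worse, then 1 to 5 fatal-only records in one arm give it (8 − 1)/20 = 35% down to (8 − 5)/20 = 15%, against 40% in the other.

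**The case against.** **Deaths are compared elsewhere.** The Safety Monitoring Committee can unblind, sees every serious adverse event and thromboembolism, and advises a halt if there is a significant excess in the intervention arm. A fatal embolism qualifies on both counts. This stands, and it rules out any claim that deaths go unmonitored. It does not repair the listed endpoint, since the committee's task is to advise on halting.

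**Some fatal events will be counted.** An embolism may be entered at grade 3 or 4 before the patient dies; 9.4.1 records outcome as a separate field; and a site may code a death as grade 4 because the scale ends there. This also stands. Exclusion is the literal reading, not a certainty for every case. But handling then depends on the person coding, which is itself a reason to settle it. Section 9.4.1 also says that all noted adverse events go into the case report form, which does not fit the eCRF restriction in 9.2.1.

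**Other comparisons could catch them.** The complications sentence in 10.2 is not limited to grades 3 and 4, and a fatal embolism might count as a death indirectly due to respiratory failure under 8.1.3. Both are possible, and neither is assured. The gap is clearest for a fatal bleed.

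**The unit of analysis.** A reader might infer that chi-square or Fisher's test would be misapplied to repeated events, because 8.1.2 speaks of a number of events. But 10.2 tabulates for each patient and only lacks a noun after its proportion, so patients are the natural unit. That is loose wording, not an invalid test.

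**Conclusion.** The point holds for the secondary safety endpoint, its adverse event capture and its planned analysis. As written, an event that is fatal without an earlier grade 3 or 4 record is not counted, and the comparison can favour the arm with more deaths. Each such patient moves an arm's rate by 5 points at 20 per arm. How many there would be cannot be said, because the protocol gives no death rate; the reversals shown rest on assumed counts. The conclusion does not depend on whether the cited CTCAE appendix, which is not among the text at hand, has a separate fatal category.

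Two stronger readings are not supported:

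- A reader might infer that the trial's safety data omit deaths. They do not, given the serious adverse event reports, the day-28 check and the committee's review by arm.
- A reader might take the poor-outcome share in the sponsor's earlier cohort (Figure 2 in section 1.2: 60 of 135, or 44%) as a sign that deaths will be common. That figure is invasive ventilation and/or death combined. The cohort also included dialysis-dependent patients and users of vitamin K antagonists at admission; this trial excludes the former and requires the latter to switch first.

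This should be corrected because the correction is cheap and specific, not because the trial's safety oversight fails.

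**What to change.** - In the summary, 8.1.2, 9.2.1 and 10.2, replace the restriction to grades 3 and 4 with grade 3 or higher, including fatal events.
- In 10.2, supply the missing unit: compare the proportion of patients in each arm with at least one such event.
- Report the day-28 deaths by arm. This also covers deaths after treatment ends, which lie outside the adverse event window in 9.2.1. Making mortality a formal secondary endpoint is optional and not needed to close the gap.

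The cost is wording in four places and one eCRF code for a fatal event. No new data are needed: deaths are already reported as serious adverse events and checked at day 28, and 12.2 lists survival status among the case report form items.

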### 9.2.2 Serious adverse events (SAEs)

A serious adverse event is any untoward medical occurrence or effect that:

- results in death;
- is life threatening (at the time of the event);
- requires hospitalisation or prolongation of existing inpatients' hospitalisation;
- results in persistent or significant disability or incapacity;
- is a congenital anomaly or birth defect; or
- any other important medical event that did not result in any of the outcomes listed above due to medical or surgical intervention but could have been based upon appropriate judgement by the investigator.

An elective hospital admission or outpatient visit will not be considered as a serious adverse event.

The investigator will report all SAEs to the sponsor without undue delay after obtaining knowledge of the events.

As symptoms in COVID-19 patients are often progressive after admission, an adverse event that prolongs hospitalization will only be considered a serious adverse events if, according to the investigator, it falls outside the natural progression of COVID-19.

Serious Adverse Events (SAEs) will be reported from the first study-related procedure until discharge from the hospital (at which time treatment will be discontinued) or until study day 28 if the patient is still admitted at that time. SAEs will be followed up for every patient on study day 28.

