### **9.5 Safety Monitoring Committee**

An independent Safety Monitoring Committee (SMC) will be appointed, including 3 individuals. Their main responsibility will be an interim analysis of all serious adverse events and occurred thromboembolisms, making the decision to halting further study procedures. A safety report including a list of all reported serious adverse events and thromboembolisms will be prepared for review by the SMC after the first 20 patients have completed follow-up and at the end of the study.

The advice(s) of the SMC will be sent to the sponsor of the study. Should the sponsor decide not to fully implement the advice of the SMC, the sponsor will send the advice to the METC that assessed the study, including a note to substantiate why (part of) the advice of the SMC will not be followed.

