#### **9.5.1 Review of safety data by the safety monitor and SMC**

A safety report including information on all reported serious adverse events and thromboembolisms will be compiled after the twentieth patient has reached the fourteenth day of the study (discontinuation of treatment) and at the end of the study. These reports will be prepared in a blinded manner by a clinical investigator and sent to the SMC and all principle investigators. During a closed session, the SMC will be able to de-blind the information prior to their review.

The responsibilities of the SMC are described in the SMC Charter. In short, the SMC will evaluate the number and nature of any SAEs and thromboembolisms that occurred during the study. In the case of statistically significant increase in the number of SAEs and thromboembolisms in the intervention group, compared to the control group, the SMC will advise the sponsor to halt the study pending further review.

The advice(s) of the SMC will only be communicated to the METC when the sponsor does not follow this. With this notification a statement will be included indicating whether the advice will be followed.

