### **10.3 Interim analysis**

There will be no interim data analysis. Fifty percent of the study patients, 10 intervention and 10 controls, has insufficient power to conduct a classical interim analysis to evaluate either the primary or secondary endpoints. Instead, the SMC will conduct a safety analysis that will focus on identifying any serious negative effect of the study intervention on patient safety.

The SMC will have access to the unblinded patient data for all serious adverse events and thromboembolisms that occurred during the trial. If a significantly higher number of SAEs or thromboembolisms occurred in the intervention group compared to the control group, the SMC will advise the sponsor to place the study on hold pending a more extensive review. In the case of such a safety hold, the trial will only be restarted after discussion with the METC that assessed the study.

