### **13.2 Synthesis**

Vitamin K supplementation has been extensively studied in healthy volunteers and several diseases including osteoporosis, cardiovascular disease and hemodialysis patients. These studies have shown no adverse effects. Toxicity studies in animals as well as observations in newborns given very high doses of vitamin K have shown no tolerability problems, no unwanted effects and no accumulation of toxic metabolites.

Vitamin K2 MK-7 is approved for sale in the European Union and freely available in The Netherlands. In a 2017 analysis the EFSA was unable to set any upper limit for the toxicity of any form of vitamin K. The current study aims to evaluate the effect of vitamin K2 MK-7 supplementation at a dose of 1000µg per day, which is similar to dosages of around 900µg

per day and 2000µg three times a week previously studied in healthy volunteers and hemodialysis patients, respectively.

Based on all available data, we were unable to predict any risks to the health of COVID-19 patients taking vitamin K2 MK-7 supplementation who are not on VKAs. During the study we will further minimize any unforeseen risks by only providing supplementation during hospital admission, when adverse events will be monitored daily and full hematology and clinical chemistry panels will be performed three times per week.

Because of its well-known role in coagulation extra attention will be paid to the development of thromboembolic complications and all patients will receive at least prophylactic dosages of heparin-based anticoagulants. Both measures are already part of standard protocol due to the high incidence of thrombotic complications in the normal progression of COVID-19.

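### The natural-progression exemption in the SAE definition can keep some non-fatal, non-life-threatening, non-thromboembolic complications out of the SMC's review during the trial

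*Protocol*

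**What the plan says.** Protocol section 9.2.2 lists the SAE criteria. One, stated without condition, is an event that "requires hospitalisation or prolongation of existing inpatients' hospitalisation". Later in the same section, because COVID-19 symptoms often progress after admission, an adverse event that prolongs the stay "will only be considered a serious adverse events if, according to the investigator, it falls outside the natural progression of COVID-19". No list of expected events, second reader or log of exempted events is given.

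On the SMC's material, section 9.5 says: "A safety report including a list of all reported serious adverse events and thromboembolisms will be prepared for review by the SMC". Section 9.5.1 says that "the SMC will evaluate the number and nature of any SAEs and thromboembolisms that occurred during the study". Section 10.3 puts the trial on hold "If a significantly higher number of SAEs or thromboembolisms occurred in the intervention group compared to the control group".

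The secondary safety endpoint in section 8.1.2 covers grade 3 and 4 events with special attention to "progression of respiratory insufficiency, thrombotic events, pulmonary embolism or deep venous thrombosis, bleeding, renal insufficiency, cardiac decompensation", and to liver abnormalities. Section 9.2.1 sends on-treatment grade 3 and 4 events to the eCRF whether or not they are SAEs. Section 10.2 compares them between groups.

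**The concern.** The exemption acts on the definition of an SAE, not only on how quickly an SAE is reported. An exempted event therefore drops out of everything built on SAEs: the SMC's list and count, the METC reports described under Toetsing Online, and the annual list in section 9.3.

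The person applying the exemption is blinded (section 8.2). For a single patient, a blinded investigator cannot tell whether the study product made a disease complication more likely or more severe. Only a comparison of the arms can show that, and the exemption takes the event away before the SMC makes its comparison. Section 9.4.2 already weighs the natural history of COVID-19 in the causality assessment. Section 9.2.2 applies the same judgement again, earlier, to decide whether the event counts at all.

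At stake is whether the SMC, after the first 20 patients, would see an excess of complications that prolong the stay without being fatal, life-threatening or thromboembolic.

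**Working it through.** **Which events can be lost.** Setting the sections side by side:

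| Type of event | Does it reach the SMC? | Source |
|---|---|---|
| Death, life-threatening event | Yes, listed SAE criteria that the exemption does not name | 9.2.2 |
| Persistent disability, or other important medical event | Yes, separate SAE criteria | 9.2.2 |
| Thromboembolism | Yes, as its own item | 9.5, 9.5.1, 10.3 |
| Special-attention event serious only through prolonged stay, judged natural progression | No stated route | 9.2.2, 9.5, 9.5.1, 10.3 |
| The same event, grade 3 or 4 and on treatment | Not stated for the SMC; kept in the eCRF and final comparison | 8.1.2, 9.2.1, 10.2 |

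Two details matter. First, section 9.2.2 does not say that the exemption is limited to events for which prolongation is the only criterion met. Second, a thromboembolism judged natural progression still reaches the SMC but could leave the METC reports and the annual SAE list. That is plausible because section 13.2 justifies its precautions as standard practice "due to the high incidence of thrombotic complications in the normal progression of COVID-19".

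**Size, as an illustration.** The protocol states no figure that this rule changes, so there is none to reproduce.

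- From the protocol: 10 patients per arm at the SMC review (section 10.3).
- Assumed: two-sided Fisher exact test at 0.05; the true proportion of patients with an SAE in each arm, p1 (vitamin K2) and p0 (placebo); and a share f of them dropped equally in both arms.

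The proportions that the SMC sees are p1(1 − f) and p0(1 − f). Power is the sum, over all pairs (t, c) with t > c and Fisher p < 0.05, of Bin(t; 10, p1(1 − f)) × Bin(c; 10, p0(1 − f)).

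The smallest significant excesses at 10 per arm are 5 v 0 (p = 0.033), 7 v 1 (p = 0.020) and 8 v 2 (p = 0.023).

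| True SAE proportions | f = 0 | f = 25% | f = 50% | f = 75% |
|---|---|---|---|---|
| 60% v 20% | 25% | 14% | 6% | 0.6% |
| 50% v 20% | 13% | 8% | 3% | 0.3% |
| 70% v 30% | 24% | 13% | 6% | 0.9% |

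For 60% v 20% with half dropped, the SMC sees 0.60 × 0.5 = 30% v 0.20 × 0.5 = 10%. The ratio stays at 3, but the difference falls from 40 to 20 percentage points and the expected counts from 6 v 2 to 3 v 1.

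With 20 per arm, as at the end of the study, the 60% v 20% row becomes 65%, 44%, 24% and 7%.

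**The case against.** The strongest reply is that little is lost. Thromboembolism, the hazard that section 13.2 singles out, has its own route to the SMC. Fatal, life-threatening and disabling events remain SAEs, as do important medical events averted by treatment, so a treated bleed or cardiac decompensation may still qualify. On-treatment grade 3 and 4 events are compared by arm at the end. Section 9.5.2 lets the study be put on hold on adverse events generally. Section 9.5.1 only summarises the SMC's duties and refers to a charter that is not at hand. The exemption is deliberate and explained. Blinding means that it should not favour an arm, and section 10.3 already concedes that 10 per arm is too few for a classical interim analysis of the endpoints.

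Most of this stands, and it limits the point. A reader might infer that the rule hides from the SMC all the complications the trial set out to watch, or that it undermines the final safety analysis. The documents do not support either: the routes just listed remain. Nor does the protocol call renal insufficiency or cardiac decompensation part of the natural course of COVID-19; it leaves that to the investigator.

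What does not fall away is the gap at the SMC. The final comparison comes too late to protect patients still being enrolled. A hold prompted by investigators rests on blinded impressions. The charter may widen what the SMC receives, but three protocol sections describe its material as SAEs and thromboembolisms only. A low-powered review is also a reason not to thin its data further.

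**Conclusion.** The concern holds in a limited form. Special-attention events that are not fatal, life-threatening or thromboembolic, and whose only seriousness criterion is a prolonged stay, can miss the SMC's by-arm review, the METC SAE reports and the annual SAE list on one blinded investigator's judgement. The consequence is reduced power to see an excess during the trial, with no expected bias toward either arm and no loss of on-treatment grade 3 and 4 events from the final analysis.

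Under the assumptions above, dropping half of the SAEs equally in both arms takes power from about 25% to about 6% for 60% v 20%. The true proportions and the share dropped are unknown. Since deaths and life-threatening events are not meant to be exempted, the share may well be smaller than the larger values tabulated. The calculation does not touch the separate thromboembolism count.

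A further inference, that a life-threatening event could be exempted because it also prolongs the stay, rests on a literal reading of an unqualified sentence. Life-threatening events are listed as SAEs in their own right, so the text does not establish that intent; it needs a clarifying clause. This is a cheap improvement worth making rather than a flaw that invalidates the design.

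**What to change.** 1. In section 9.2.2, state that the exemption applies only where prolonged stay is the sole seriousness criterion met, and that it exempts the event only from expedited reporting to the METC. Align the text under Toetsing Online, which at present sends every SAE to the METC within fixed times.
2. Record each such event as an SAE in the eCRF with a flag such as 'consistent with COVID-19 progression'. It then also enters the annual list in section 9.3.
3. In sections 9.5 and 9.5.1, add to the SMC report the flagged and unflagged SAEs and the grade 3 and 4 special-attention events already collected. List them by treatment number, so that the SMC can split them by arm after unblinding in its closed session while the investigator who prepares the report stays blinded.

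The cost is wording in these sections, one extra eCRF field, some added data entry and a longer SMC listing, in a 40-patient trial at one hospital. Expedited reporting need not increase, so the purpose of the exemption is kept.
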